**Discussion:**

The study aims to investigate the impact of PT in older women at risk of sarcopenia. The expected results are that PT will significantly improve functionality and body composition compared to other forms of exercise (MT) and no physical activity. The results may represent a significant advance in understanding and addressing sarcopenia before it becomes established, providing preventive treatment and new tools whose clinical applicability has been studied.

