#### Sample size

Sample size was calculated for the main study variables, 5STS and HG. The minimum detectable change in similar populations and interventions was 2.5 points (a decrease in 5STS and an increase in HG) to consider a real change beyond measurement error [30, 31]. The study used GRANMO version 7.12 of April 2012. Assuming three groups, with an alpha risk of 0.05 and a beta risk of 0.2 in a bilateral contrast. A loss-to-follow-up rate of 20% was estimated, given that the intervention was extensive and older people are known to have lower adherence to physical activity programs [32]. It was concluded that 105 subjects would be needed among the three groups with a 1:1:1 ratio to detect a difference equal to or greater than 2.5 units, assuming a standard deviation of 5 units.

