Five-Repetition-Sit-To-Stand Test (5STS): this is a functional test that assesses a person’s ability to stand up and sit down from a chair for five times without using the arms (lower extremity strength). The 5STS has been shown to be a more sensitive and specific measure than the original test [33]. It also offers excellent test-retest reliability (0.89) [34].Hand grip test (HG): is a quick, easy and inexpensive test that measures hand grip strength. This test is recognized in clinical practice and in the literature as a standard instrument for measuring HG [15]. It will be performed with the Jamar Plus device in standing position and with the elbow flexed to 90 degrees, which has been shown to have excellent test-retest reproducibility (r>0.80) and excellent inter-observer reliability (r = 0.98) [35, 36].**Secondary functional variables**: the Sarc-f questionnaire will be administered as a rapid diagnostic test for sarcopenia that predicts the need for further evaluation [37]. Physical activity will be monitored through the International Physical Activity Questionnaires (IPAQ) [38]. The Short Physical Performance Battery (SPPB), as it is a rapid, objective three-test physical function test that measures lower extremity strength, gait speed, and balance [39]. The Timed Up&Go (TUG), which is a predictor of frailty and falls, widely used in geriatric research to measure balance and mobility in older people [40]. Gait speed, which is a simple, objective and valid measure of human gait performance that has been used in a variety of settings and is recommended for use as a "vital sign" of health [41]. Two-minute step test to measure aerobic capacity in older adults [42]. The number of falls will also be recorded one year before the start and during the intervention.**Secondary body composition variables**: electrical bioimpedance (TANITA BC-418) will be used to measure most body composition parameters. The total percentage of fat (BF%) and muscle, which is important for general health, will be calculated [43]. Additionally, appendicular muscle mass (ASM) will be calculated, as it is one of the most important variables in the diagnosis of sarcopenia today. It is generally adjusted for height to obtain the appendicular muscle mass index (SMI) (ASM/height^2^). In order to predict the risk of developing chronic diseases, measurements of visceral fat, waist circumference (WC), and body mass index (BMI) (weight/height^2^) will be taken [15]. Height will be measured with a height rod.

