### Data analysis

Statistical analysis will be performed using an intention-to-treat (ITT) approach. Baseline differences between groups will be tested using normality plots and the Kolmogorov-Smirnov test. Homogeneity between groups will be assessed using Levene’s test, thus ensuring successful randomisation. Missing data will be handled using the imputation method of the last observation carried forward. It will be decided to keep outliers in the analysis, as they may represent legitimate outliers or relevant information, which will be discussed in the future study.

A descriptive analysis of the dependent and independent variables of each group will be carried out. Quantitative variables will be expressed as mean ± standard deviation, while qualitative variables will be presented as frequency distributions and percentages.

To assess the effect of the interventions on the study variables in each group, multivariate analysis of variance (MANOVA) will be used as the main method. The variables will be grouped into two large blocks: those measuring functionality (HG, 5STS, GS, TUG, Two-minute step test and SPPB) and those measuring body composition (weight, WC, BF%, visceral fat, ASM, SMI and BMI). Subsequently, MANOVA will be performed on the difference in means after the intervention, using time as an intra-group factor and type of intervention as an inter-group factor. To graphically represent the MANOVA, the canonical Biplot will be displayed, including the confidence circles representing the set of variables in each intervention group. If the circles do not overlap, it can be concluded that there are significant differences between the groups.

To verify the results of the MANOVA, differences between groups for each quantitative variable, both functional and body composition, will be analysed using the repeated measures univariate analysis of variance (ANOVA) test for normal and homogeneous variables or the Kruskal-Wallis test for non-normal or heterogeneous variables. As an additional method, pairwise comparisons will be performed using Bonferroni’s test for normal and homogeneous variables and Dunn’s test for non-normal and heterogeneous variables to determine between which groups there are significant differences.

The effect size in ANOVA of the results obtained in each group will be measured by eta squared (η^2^). Values around 0.01 indicate a small effect size, around 0.06 a medium effect size, and 0.14 or more a large effect size.

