A 95% confidence interval will be used to establish any differences, and statistical significance will be reported for all differences with p < 0.05 (bilateral). All statistical analyses will be performed using IBM SPSS for Windows (version 26.0, Armonk, NY. IBM. Corp.).

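### Eleven secondary variables are each tested at p < 0.05 with no control across variables and no stated link to the block MANOVA, although significant gains in body composition, a domain with only secondary variables, are expected

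*Protocol article*

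**What the plan says.** Under Description of the variables, the protocol article names 5STS and HG as primary and the rest as secondary. All of body composition falls in the second class: "Secondary body composition variables: electrical bioimpedance (TANITA BC-418) will be used to measure most body composition parameters". The Sample size section agrees: "Sample size was calculated for the main study variables, 5STS and HG".

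The Data analysis section then regroups the variables without using that ranking. One block holds "those measuring functionality (HG, 5STS, GS, TUG, Two-minute step test and SPPB"), the other "those measuring body composition (weight, WC, BF%, visceral fat, ASM, SMI and BMI"). MANOVA on the two blocks is the principal method. As a check on it, "differences between groups for each quantitative variable, both functional and body composition, will be analysed using the repeated measures univariate analysis of variance", with Kruskal-Wallis as the alternative. Pairwise comparisons by Bonferroni or Dunn follow as an extra step. The closing rule is general: "statistical significance will be reported for all differences with p < 0.05 (bilateral").

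The Abstract states the expected result as "PT will significantly improve functionality and body composition compared to other forms of exercise (MT) and no physical activity", and the main Discussion repeats this as a hypothesis.

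**The concern.** The significance rule covers all differences, so a secondary variable earns the word significant on the same terms as a primary one. The Bonferroni or Dunn step protects against testing three pairs of arms within one variable. It does nothing about testing many variables. No order of testing, split of alpha or exploratory label is given for the secondary variables.

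This matters because the stated expectation has two halves, functionality and body composition, and the second contains only secondary variables. A single chance result, for example on waist circumference, could be reported as a significant benefit of power training on body composition even if 5STS and HG both show nothing.

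**Working it through.** **No plan figure to reproduce.** The protocol states no error rate across variables, so the check starts from its per-test level.

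**Inputs from the protocol**
- Level per test: 0.05, two-sided (Data analysis).
- Variables in the blocks: 6 functional + 7 body composition = 13. Less the two primaries, 13 − 2 = 11 secondaries: 6 − 2 = 4 functional (gait speed, TUG, two-minute step test, SPPB) and 7 body composition.
- Size: 105 in three equal arms, so 105/3 = 35 per arm. After the planned 20% loss, 35 × 0.8 = 28 per arm.

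**Assumption.** The correlations between changes in these variables are not in the document, so a range is shown.

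**Step 1: independence, no true effect, no gating.** P(at least one p < 0.05) = 1 − 0.95^k.
- k = 11: 1 − 0.95^11 = 43.1%
- k = 7 (body composition): 1 − 0.95^7 = 30.2%

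**Step 2: correlated variables, no true effect, no gating.** With two time points, the arm-by-time test of a repeated measures ANOVA is the one-way F test on the change score. Simulating that test with equally correlated normal changes and 28 per arm gives the following. Repeat runs differ by a point or two, and runs with 35 per arm gave similar values for the 11 variables.

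| Assumed correlation | 11 secondaries | 7 body composition |
|---|---|---|
| 0 | about 43% | about 30% to 31% |
| 0.3 | about 37% | about 28% |
| 0.5 | about 31% to 32% | about 24% |
| 0.8 | about 18% | about 15% to 17% |

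**Step 3: near-duplicates.** SMI is ASM over height squared and BMI is weight over height squared. Height hardly changes over 32 weeks, so each pair is close to one test. Setting those pairs near 0.97 to 0.98, with 0.3 to 0.7 elsewhere in the block, gives about 28% to 37% for the 11 variables and about 16% to 23% for body composition.

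**Step 4: power training contrasts only.** Counting only the two contrasts that involve power training, each at 0.05/3, the chance of at least one false result over 11 variables is about 21% at correlation 0.5 (30% at 0, 13% at 0.8). The correction within a variable does not remove the problem.

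**Step 5: univariate tests read only after a significant block MANOVA.**
- No effect on any body composition variable: a false univariate result in that block occurs in about 2% to 5% of trials.
- No effect on any variable in either block: if the blocks are independent, the two gates bound the rate at 1 − 0.95^2 = 9.75%.
- A real effect of 1 SD for power training on one body composition variable, correlation 0.5, 28 per arm: the chance of a false ANOVA among the other six is about 21%, with or without the gate, because the real effect opens it.

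The functional block contains both primaries, so a real effect on 5STS or HG would open the gate for its four secondaries in the same way.

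**The case against.** The strongest reply is that MANOVA is the principal method, with the univariate tests following as a check and the pairwise tests as an extra. That can be read as omnibus test first, follow-up second. Body composition would then be one block test, not seven, and under a complete null the error is small (Step 5). This stands in part. A reader might infer that the plan runs the univariate tests regardless of the MANOVA, but the text does not say so. It is silent. The fair criticism is that the dependence is unstated, and that even if stated it would not protect the remaining variables once one has a real effect.

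A reader might also infer that the plan fails to rank its outcomes. It does rank them: the primary and secondary labels are explicit, and the sample size rests on the two primaries. What is missing is any consequence of those labels for what may be called significant.

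It can also be said that unadjusted secondary tests are common, that their handling is often left to an analysis plan, and that the Abstract and Discussion state expectations, not decision rules. All true. The point therefore rests on what the article does fix: a significance rule for all differences, beside an expectation of significant gains in a domain with no primary variable. An analysis plan that confined claims to the primaries would contradict that rule.

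**Conclusion.** The point holds in a limited form. As written, 11 secondary variables can each be declared significant at 0.05 with no control across variables. With no true effect and no gating, the chance of at least one false ANOVA is about 43% under independence and about 18% to 37% at assumed correlations of 0.8 to 0.3. For body composition alone it is about 15% to 31%, and treating weight with BMI and ASM with SMI as near-duplicates puts it within the lower part of that range.

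A reader might want to quote one figure, such as 31%, as a property of this protocol. The document does not support that: the figure needs an assumed correlation of about 0.5, and it applies only if the univariate tests are not gated. Across the assumed correlations, every ungated figure is at least about three times the 5% level (15/5 = 3). If gating is intended, the body composition rate is about 2% to 5% under a complete null but about 21% when one variable in the block has a real effect. The defect is one of wording and interpretation. It does not affect the design or the data.

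**What to change.** In the protocol article:
1. In Data analysis, replace the general significance sentence with one that limits confirmatory significance claims to 5STS and HG.
2. State that univariate and pairwise results for all other variables are supportive or exploratory, are reported as between-arm differences with 95% confidence intervals, and are read only after a significant MANOVA for their block. The label is needed as well as the gate, because the gate alone fails when one variable in the block has a real effect.
3. State that a claim about body composition rests on the body composition block MANOVA, or on one variable named in advance, and not on any single univariate result. A gate worded as success on the primary test would not work, since there are two primary variables and the article does not say how they combine.
4. Align the expected result in the Abstract and the hypothesis in the Discussion with these statements.

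The cost is wording only, with no new data and no new analyses. The downside is that a single secondary result can no longer be announced as a confirmed effect.

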### Ethical aspects

The study was approved by the Ethical Committee for Research with Medicines of the Salamanca Health Area with the code PI 2023061317, having obtained the prior written informed consent of the study subjects and in conformance with the Helsinki Declaration [29].

The participants, before the start of the study, will be informed of the objectives of the project and the risks and benefits of the explorations that will be carried out; subsequently, they must sign the informed consent. In the carried out way, the confidentiality of the subjects included in the study will be guaranteed at all times, in accordance with the provisions of Organic Law 3/2018, of December 5, on the Protection of Personal Data and guarantee of digital rights, under the conditions established by Law 14/2007, of July 3, on biomedical research and Regulation (EU) 2016/679 of the European Parliament and of the Council, of April 27, 2016, on Data Protection (RGPD). Data and information will not be shared with third parties. Each participant will be coded, so their personal data will not be known. Only those who perform the statistical analysis will have access to the database.

Significant modifications to the protocol (such as changes in the tools of evaluation, modifications to the selection criteria or to the interventions) will be communicated immediately to the Ethics Committee.

And since this is a randomised clinical trial, it follows the CONSORT guidelines, and it was registered. TRIAL REGISTRATION: ClinicalTrials.gov; ID: NCT05870046.

### Rigour

This study has been developed in accordance with the recommendations supported by the SPIRIT Declaration 2013 regarding the essential content of a clinical trial protocol (see S1 Table). Furthermore, the study design follows the guidelines established by the CONSORT 2010 guidelines for the execution of parallel group randomized controlled clinical trials.

For effective description and replication of the proposed intervention, the TIDieR checklist is included as an additional tool (see S3 Table).

Upon completion of the study, the data collected here will be made available to those investigators who request it through FAIR sharing of research data repositories at https://www.re3data.org/.

### Human and material resources

The personal resources are a total of 18 people belonging to the project linked to the GRP. The necessary and adequate spaces for carrying out the evaluation visits and intervention sessions will be the Faculty of Nursing and Physiotherapy of the University of Salamanca and the Centers for the Elderly of the City of Salamanca dependent on the Salamanca City Council.

The material resources used during the study are stopwatches, tape measures, furniture, blood pressure monitor (OMRON® M7 Intelli IT, HEM-7361T-EBK), measuring rod, hand dynamometer (Jamar® Plus Hand Dynamometer), body composition bioanalyzer (Bioimpedance meter TANITA® BC-418), linear encoder (ADR® Encoder), SARC-F questionnaires, material for the exercise sessions (cones, ladders and weights) and IBM SPSS software statistics v. 28 .0

## Discussion

The study aims to investigate the impact of PT on older women at risk of sarcopenia. It is hypothesized that PT can reverse the probable sarcopenic state in women over 65 years of age, acting as an effective preventive therapy that eliminates the risk of sarcopenia and prevents its associated factors. Additionally, it is hypothesized that PT will significantly enhance functionality and body composition in comparison to other forms of exercise and no physical activity.

It is important to note that sarcopenia, which is commonly associated with frailty, is also independently linked to an increased risk of falls [45, 46]. By preventing sarcopenia, hospitalizations, institutionalizations, and other associated adverse effects can be indirectly avoided. The scientific community has demonstrated with high certainty that exercise programs reduce the rate and number of falls in the elderly [47]. Therefore, we expect both PT and other forms of exercise to improve this aspect, with a particularly optimistic expectation for PT.

Meta-analyses have been conducted to evaluate the effect of PT on healthy older adults [25, 26]. Similarly, meta-analyses have been performed to assess the impact of RT on function and body composition in people with sarcopenia [15, 48, 49]. However, this study is the first of its kind to investigate older women with probable sarcopenia according to EWGSOP2 diagnostic criteria. This study aims to address a gap in scientific knowledge by investigating an understudied area. To our knowledge, only one other clinical trial has evaluated the effect of RT in older women and men with probable sarcopenia. However, this trial only assessed appendicular lean mass and BF% [50].

This study investigates the effect of PT as a preventive treatment in older women with probable sarcopenia. It represents an important advancement in understanding and addressing this condition, as scientific evidence on the various forms of preventive treatment available for sarcopenia has been insufficient. However, this study’s findings will not only fill the knowledge gap but also support the recommendations issued by the EWGSOP2 in 2019. This will provide a solid basis for implementing effective prevention and treatment strategies for sarcopenia in older women [15].

In addition, it is important to consider that the PT exercise program in this study is designed in such a way that any older adult can carry it out at home safely, without requiring any material, and the progression of the load is based on the perception of effort. Therefore, at the end of the program, people will be able to continue doing it at home without the need to calculate the MRI or incur additional expenses. This aspect is of great importance, as it facilitates the transfer of research to society, allowing older adults to benefit from the potential effects of power training when they are in states of sarcopenia probable.

### Limitations

The study protocol has limitations that should be communicated to inform the interpretation of the results and the design of future research. Although the study follows all CONSORT recommendations, participating subjects will not be blinded to the intervention due to the nature of the intervention. Given the variability of the factors that may affect this population group, not all of them will be assessed, including dietary patterns and different diseases such as diabetes. The expected results cannot be extrapolated to the general population, to other population groups (such as hospitalized or institutionalized older adults) or to different environments or city. This sample was chosen because older women, the population group that lives in the community, probably represent the most people who may be at risk of sarcopenia. We have prioritized obtaining results with a homogeneous sample over generalizing them to the general population.

Progression during the intervention will be based on each participant’s perception of effort, which may introduce biases as some participants may overestimate or underestimate their effort. Although the physical therapist will instruct participants on how to determine their perceived exertion, it is important to note that their unfamiliarity with this method may affect the results.

### Dissemination plan

The results of this clinical trial will be published in high impact journals of different specialties with the intention of achieving maximum visibility. Knowledge will also be transferred to society through conferences for older adults and dissemination through social networks and the media.

### Future perspectives

The project has the potential to bring practical benefits and transfer results to clinical practice in physiotherapy. It could also have a positive impact on general health, as well as the economic and social spheres. The effect of PT should be investigated in more population groups (men, confirmed or severe sarcopenia) to be able to generalize the results to the general population.

In recent years, there has been increasing interest in studying sarcopenia and aging, including diagnosis and possible interventions to improve this condition. It is widely accepted that a healthy lifestyle, including a balanced diet and regular exercise, is essential to mitigate the negative effects of clinical conditions. The aim of this study is to investigate the effectiveness of PT and MT in improving functional and body composition parameters as a means of preventing sarcopenia.

In 2019, EWGSOP recommended that healthcare professionals take steps to promote early detection and treatment of sarcopenia in patients at risk. It is recommended that the diagnosis, treatment, and prevention of sarcopenia be included in routine clinical practice. Sarcopenia is becoming a major problem for the National Health System, leading to increased healthcare costs due to the aging population. Therefore, it is important to promote cost-effective interventions, such as PT or MT that can reduce these costs and improve the quality of life for those at risk.

